## METHODS

### Study design

The present cohort study will be conducted in older adults diagnosed with frailty. A multicenter study will be conducted among the day care centers and nursing homes Residencia de Nuestra Señora de la Soledad y del Carmen (Colmenar Viejo, Madrid), Residencia San Camilo (Tres Cantos, Madrid), Centro de Día San Camilo (Tres Cantos, Madrid), Residencia San Luis de Gonzaga ([name]), Hospital Príncipe de Asturias (Alcalá de Henares, Madrid) and Hospital Puerta de Hierro (Majadahonda, Madrid) from their diagnosis between April 2024 and June 2025, in the country of Spain. The study protocol was approved by the Research Ethics Committee of the Hospital Universitario Puerta de Hierro, Madrid, Spain (Act nº 18/2023). In addition, the study was registered with https://clinicaltrials.gov/ (NCT06218121), and will be conducted following the Strengthening the Reporting of Observational Studies in Epidemiology (STROBE) statement and checklist [17]. According to the Declaration of Helsinki, all patients will sign an informed consent form before inclusion and must agree that their clinical information will be published anonymously.

### Samples

A diagnosis of signs and symptoms of frailty by a geriatric physician from the research group ([name]) and the centers' medical staff will be used as the main inclusion criterion. Frailty will be assessed and diagnosed using the frailty phenotype and the Clinical Frailty Scale.

As exclusion criteria:

Acute myocardial infarction in the last 3 months and/or unstable angina pectoris.Uncontrolled arrhythmia, recent thromboembolism, and terminal illness.Patients with recent unloading of lower limbs (LL), or with UL/LL fractures in the last three months.Patients with a functional gait index of 1 (Inability to walk).Severe pain (7/10 Numeric Pain Rating Scale, NPRS).Previous neuromuscular pathology presenting with weakness.Medication that does not allow the patient's actual muscle reaction to be assessed.Severe cognitive impairment that would prevent collaboration and understanding of the tests to be performed.Cardiovascularly unstable patients and uncontrolled arterial hypertension.

For the cohort study, 500 frail older adult patients will be evaluated by means of instrumental and functional tests that assess their functional capacity, in addition to ultrasound imaging to study sarcopenia and nutrition, as well as psychological variables. The correlation between all functional, ultrasound, nutritional, and psychological variables will be analyzed. Through the Global Leadership Initiative on Malnutrition (GLIM) criteria diagnosis, anthropometric data (weight, height, and Body Mass Index-BMI) as well as analytical data including inflammation information (CRP and albumin) will be used to reach a diagnosis that allows comparison/correlation with the rest of the variable parameters [18]. The GLIM criteria provide a diagnostic system that has been accepted by the main international scientific societies in the field of clinical nutrition [19–21]. All available information will be collected during the follow-up in order to generate Machine Learning on the objective evolution and symptomatology of these patients, generating profiles that facilitate the most accurate and appropriate treatment for each patient.

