## BACKGROUND

### The concept of frailty

Between 2015 and 2050, the global population aged 60 and above is projected to rise from 12% to 22% [1]. Advancing age correlates with a higher incidence of chronic ailments, frailty, dependency, and elevated healthcare expenditures [2–4]. Frailty is a complex medical condition marked by diminished strength, endurance, and physiological functions, heightening an individual's susceptibility to adverse outcomes, including mortality [5]. Its prevalence among the elderly ranges from 8% to 16% and is often intertwined with dementia [6] or cardiovascular disease [7]. Moreover, frailty in older adults frequently coexists with sarcopenia, an age-related syndrome characterized by progressive muscle mass and strength decline, heightening the risk of physical impairment and diminished quality of life [8].

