### Statistical analysis

The R program version 4.3.1 will be used for statistical analysis. The level of significance will be set at *p* < 0.05. The distribution of quantitative variables, both baseline and outcome, will be tested with the Kolmogorov-Smirnov test with Lilliefors correction. Qualitative variables will be described in absolute values and frequencies and quantitative variables with mean and standard deviation.

Baseline and outcome variables differences using Barthel Index (BI) score dichotomized between dependent (BI < 60) and independent (BI > 60) patients [31] using *T*-test or U-Mann-Whitney for quantitative variables (depending on their distribution) and Fisher exact test for qualitative variables.

A multivariate analysis will be performed with a machine learning model through principal analysis using logistic regression, applying the model to 75% of the subjects and evaluating its accuracy in the remaining 25%, with the objective of creating a trained model that allows the development of therapeutic intervention plans that enable both the evaluation and treatment of patients. Model will be controlled by baseline variables with significant differences in univariate analysis.

Model will be constructed with dichotomized Barthel index as dependent variable and manual grip strength, EuroQoL-5D, NPRS, cross sectional area and thickness of the rectus femoris, STAI, TSK and BDI as explanatory variable. Logistic model will be selected instead of others used in machine learning (e.g. Random Forest, Support Vector Machines or Gradient Boosting) because it is computationally more efficient and faster and more easily interpretable.

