### Sample size calculation

The sample size was carried out based on the main objective and analysis of the study to evaluate which variables influence the level of dependence/independence through a multivariate logistic regression model, with Barthel index dichotomize as dependent variable, and manual grip strength, EuroQoL-5D, NPRS, cross sectional area and thickness of the rectus femoris, STAI, TSK and BDI as explanatory variable, for which a sample of 500 subjects was recommended according to Bujang et al. formula (100 + 50 × number of explanatory variables) and minimum sample size for logistic regression models [38–40].

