### Implications and limitations

The potential implications of this study are substantial for both clinical practice and public health. The integration of ultrasound-derived muscle parameters with functional and psychological assessments, analyzed through machine learning, offers a scalable and cost-effective approach for the early detection of frailty. This may enable clinicians to stratify risk and tailor interventions in community-dwelling and institutionalized older adults, enhancing preventive care and reducing adverse outcomes associated with frailty.

Nonetheless, the study presents several limitations. First, the ultrasound measurements are operator-dependent, which introduces a risk of inter-rater variability. To mitigate this, we ensured strict standardization of procedures and training across all sites, along with reliability testing. Second, although the machine learning model will be internally validated using cross-validation and a separate test set, no external validation in a different population is planned in this protocol. Third, as participants are recruited by convenience sampling from institutional settings, there is a potential for selection bias and limited generalizability to broader older adult populations. Fourth, the accuracy of ultrasound imaging can be affected by the presence of subcutaneous fat, particularly in individuals with overweight or obesity. Excess adipose tissue may reduce image clarity, impairing precise delineation of muscle boundaries and affecting measurements of thickness and cross-sectional area. To address this limitation, we use a standardized acquisition protocol with high-frequency probes and minimal compression, and we plan to include anthropometric indicators such as body mass index (BMI) in the analysis to statistically adjust for this potential confounder. Lastly, while the current model focuses on predicting dependence based on the Barthel Index, other frailty dimensions (e.g., cognitive, social) may not be fully captured. These limitations will be addressed in future longitudinal studies with broader inclusion criteria and external validation.

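### Milder cognitive impairment may enter the cohort, but no cognitive measure is scheduled and the explanatory model names none, so effects of its five self-reported predictors may be partly confounded

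*Protocol article*

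**What the plan says.** All references are to the protocol article.

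- **Eligibility (Samples).** The cognitive exclusion is "Severe cognitive impairment that would prevent collaboration and understanding of the tests to be performed". No instrument or cut-off is named. Four of the six listed sites are nursing homes or a day centre, and the background says that frailty "is often intertwined with dementia".
- **Data collected.** Neither Materials, nor Sample characterization, nor Table 1 lists a cognitive test. Table 1 does list medical history and comorbidity.
- **Main model (Statistical analysis).** "Model will be constructed with dichotomized Barthel index as dependent variable", with "manual grip strength, EuroQoL-5D, NPRS, cross sectional area and thickness of the rectus femoris, STAI, TSK and BDI as explanatory variable".
- **Aim (Sample size calculation).** The model is meant to "evaluate which variables influence the level of dependence/independence through a multivariate logistic regression model".
- **Further covariates.** The rule is: "Model will be controlled by baseline variables with significant differences in univariate analysis". The only adjustment named in advance is for body size: "we plan to include anthropometric indicators such as body mass index (BMI) in the analysis" (Implications and limitations).
- **Cognition as a limitation.** The same section concedes that "other frailty dimensions (e.g., cognitive, social) may not be fully captured".

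**The concern.** EuroQol-5D, NPRS, STAI, TSK and BDI all rest on the participant's own answers. A participant with mild or moderate impairment may answer them differently and may also need more help with daily activities. If both happen, these scores partly stand in for cognition in a model of Barthel dependence. Anxiety, depression, fear of movement or pain could then look like determinants of dependence when they are not, or real effects could be hidden.

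This matters because the aim is explanatory and the article wants the results to inform intervention plans. For prediction alone, a proxy for cognition would do less harm. A later analysis plan can choose covariates only from what was recorded, so a cognitive level that is never collected cannot be restored.

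**Working it through.** **1. The plan's own figure.** The rule is 100 + 50 × number of explanatory variables. With eight variables, 100 + 50 × 8 = 500, which reproduces the stated sample size.

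**2. Count of predictors.** Self-reported: EuroQol-5D, NPRS, STAI, TSK, BDI (5). Measured: grip strength, rectus femoris cross-sectional area, rectus femoris thickness (3). So 5 of 8 are self-reported.

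**3. How cognition could reach the model.**
- As a named predictor: no.
- As a named adjustment: no; only anthropometry is named.
- Through the univariate screen: only as a dementia diagnosis, if one is recorded under medical history or comorbidity and differs significantly between the Barthel groups. The elastic net step could then remove it.
- As a graded level: no route, because none is among the listed variables.

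**4. Size, by simulation.** The article gives no inputs for this, so all of the following are assumptions: 30–40% of participants with milder impairment; odds of dependence doubled or tripled by impairment; each questionnaire shifted by 0.3, 0.5 or 0.8 SD; no true effect of any questionnaire. N = 500, two-sided Wald test at 0.05.

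*One questionnaire fitted alone:*

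| Shift | Odds × 2 | Odds × 3 | Spurious OR per SD (odds × 3) |
|---|---|---|---|
| 0.3 SD | 7–10% | 10–14% | 1.07 |
| 0.5 SD | 12% | 23–28% | 1.13 |
| 0.8 SD | 21–23% | 42–51% | 1.21 |

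A repeat gave 7–55% over the whole grid. This is not the planned model, which enters the questionnaires together.

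*Five questionnaires fitted jointly, all shifted, within-group correlation r:*
- r = 0.3 to 0.5: about 5–11% false positives per questionnaire; mean spurious OR per SD 1.02–1.07.
- r = 0: up to about 26%. A repeat with 40% dependent (assumed) gave 28% in the same corner, so roughly a quarter is as exact as this figure gets.

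The reason for the drop: with five equally correlated, equally shifted scores, the within-group partial contribution of each is proportional to shift / (1 + 4r). The divisor is 1 + 4 × 0.3 = 2.2 at r = 0.3 and 1 + 4 × 0.5 = 3.0 at r = 0.5. Correlation also widens the standard errors.

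*A continuous cognition score instead* (OR 1.5, 2.0 or 2.5 per SD; correlation 0.2–0.4 with each questionnaire; questionnaires linked only through cognition; 30% or 50% dependent): 11–18%, 22–38% and 28–56% per questionnaire.

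The two sets agree once put on one scale. A binary factor with share 0.3 has SD √(0.3 × 0.7) = 0.458, so tripled odds equal exp(0.458 × ln 3) = 1.65 per SD. With share 0.4 the SD is 0.490 and the result is 1.71. The rows at 2.0 and 2.5 therefore assume much stronger confounding, and none of them allows the questionnaires any other correlation.

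**5. With cognition in the model.** The false-positive rate returns to about 3–7% in all versions.

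**6. Sample-size rule after the change.** One added term: 100 + 50 × 9 = 550. A three-level grade coded as two terms: 100 + 50 × 10 = 600.

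**The case against.** The case on the other side has real force.

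- **The existing screen may already help.** If a dementia diagnosis is recorded and carries doubled odds, a Fisher test at 0.05 selects it in 91–96% of simulated samples, and in about 100% with tripled odds. The false-positive rate with it in the model is then 3–7%. A reader might infer that cognition is wholly shut out of the model; the article does not support that. What remains is that the route depends on the data, misses undiagnosed or graded impairment, and can be undone by the elastic net.
- **Large error rates do not describe this model.** A reader might infer false-positive rates near 50%. Those come from one questionnaire fitted alone, or from strong confounding with otherwise uncorrelated questionnaires. No simulation included the elastic net, the VIF step or the data split. The listed outputs are discrimination measures and variable importance, so a Wald error rate is only an index of the bias.
- **The causal premise is external.** Nothing in the article says that cognition lowers the Barthel score or shifts these questionnaires. The link to dementia concerns frailty in general. The premise is plausible, not documented.
- **Safeguards exist.** The exclusion is worded by ability to understand the tests, and participants sign consent. This limits unreliable answers, but it does not prevent confounding by milder impairment.
- **The article is condensed.** Figure 1 is not shown and the full protocol may hold more. Even so, Table 1 is detailed and has no cognitive item.
- **The limitation is acknowledged.** It is acknowledged as a frailty dimension that may be missed, not as a confounder of the predictors.

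**Conclusion.** The concern holds in a limited form. Milder impairment can enter, no cognitive measure is listed, and the explanatory model has no prespecified cognitive term while five of its eight predictors are self-reported. If cognition affects both sides, psychological and pain effects are partly confounded, in a direction the article does not let us fix.

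The best estimate for the joint model is modest: about 5–11% false positives per null questionnaire against 5%, with a spurious OR per SD of 1.02–1.07. The upper figure is about 26% if the questionnaires are otherwise uncorrelated. These figures rest on assumed prevalence, effect sizes and correlations. This is a worthwhile, low-cost improvement rather than a flaw that invalidates the analysis.

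**What to change.** - At the eligibility review, record any dementia diagnosis and any cognitive score or grade already on file. If enrolment has finished, retrieve these from records where possible.
- Include that variable in the main model as a prespecified covariate, regardless of univariate significance and outside the elastic net penalty.
- Add a sensitivity analysis without participants who have a dementia diagnosis.
- State in the limitations that cognition may confound the self-reported predictors.

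**Cost.** One data field, one model term and one extra analysis, with no new procedure for participants. Eligibility requires only a judgement of severe or not severe, so it should not be assumed that a none/mild/moderate grade already exists for everyone. Scores may be missing or come from different instruments, and a diagnosis indicator or coarse grade may be all that is usable.

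Under the article's rule a ninth variable gives 550. The statement that 500 meets that rule should be qualified; this is not a reason to enrol more, since the plan already admits screened covariates and BMI beyond the eight.

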### Materials

Measurement variables evaluated in patients include:

Manual grip strength: The peak grip force was measured using a hydraulic hand dynamometer (JAMAR, Sammons Preston Rolyan, Sammons Court Bolingbrook, IL, USA) across a range of 0 to 90 kg. This device has been validated, shown to be reproducible, and deemed reliable for assessing grip strength in older individuals [22].Quality of life: measured with the EuroQol-5D, where mobility, personal care, daily activities, pain/discomfort, anxiety, or depression are assessed [23].Barthel Index: Assesses the level of independence of the subject with respect to the performance of activities of daily living [24].Trunk control test: Designed for the assessment of the patient's motor impairment [25].Intensity of Pain: Using the NPRS [26].Ultrasound image: The cross-sectional area and thickness of the rectus femoris muscle will be measured. In addition, contraction potential, contraction-relaxation velocity data will be taken by M-Mode ultrasound [27].The State-Trait Anxiety Inventory (STAI): Assessing state and trait anxiety [28].Kinesiophobia (TSK): Using the Tampa Kinesiophobia Scale, measuring fear of movement [29].Beck Depression Inventory (BDI): It measures depressive symptoms and the severity of depression [30].

Figure 1 illustrates the collection of variables in the older adult population of the study. Figure 2 summarizes the study workflow, from participant recruitment and assessments to the machine learning pipeline for prediction and analysis.

**Figure 1 f1:**
[figure not shown]
**Collection of variables in the older adult population of the study.** This visual summarizes the clinical, psychological, functional, and ultrasound-based variables collected in the frail elderly population.

**Figure 2 f2:**
[figure not shown]
**Flowchart of the study protocol.** The diagram outlines the sequential phases of the multicenter cohort study, including participant recruitment, baseline assessments, data preprocessing, machine learning pipeline, and model outputs.

### Statistical analysis

The R program version 4.3.1 will be used for statistical analysis. The level of significance will be set at *p* < 0.05. The distribution of quantitative variables, both baseline and outcome, will be tested with the Kolmogorov-Smirnov test with Lilliefors correction. Qualitative variables will be described in absolute values and frequencies and quantitative variables with mean and standard deviation.

Baseline and outcome variables differences using Barthel Index (BI) score dichotomized between dependent (BI < 60) and independent (BI > 60) patients [31] using *T*-test or U-Mann-Whitney for quantitative variables (depending on their distribution) and Fisher exact test for qualitative variables.

A multivariate analysis will be performed with a machine learning model through principal analysis using logistic regression, applying the model to 75% of the subjects and evaluating its accuracy in the remaining 25%, with the objective of creating a trained model that allows the development of therapeutic intervention plans that enable both the evaluation and treatment of patients. Model will be controlled by baseline variables with significant differences in univariate analysis.

Model will be constructed with dichotomized Barthel index as dependent variable and manual grip strength, EuroQoL-5D, NPRS, cross sectional area and thickness of the rectus femoris, STAI, TSK and BDI as explanatory variable. Logistic model will be selected instead of others used in machine learning (e.g. Random Forest, Support Vector Machines or Gradient Boosting) because it is computationally more efficient and faster and more easily interpretable.

We will follow these steps to perform model: a) delete variables with high multicollinearity that is, presenting a Variance Inflation Factor (VIF) highest than 5, b) check model assumptions, if residuals are not normality distributed, they will be transformed with log or Box-Cox transformation, if they present heteroskedasticity or residuals remain not normally distributed, robust bootstrap model will be applied, c) random split of data set into training (75%) and test (25%), c) train the model with cross validation (5-folders will be applied) and elastic net features selection (it combines lasso and ridge features selection), e) model performance will be assessed with confusion matrix, Receiver Operating Characteristic (ROC) curve and calculation of Area Under a Curve (AUC), sensitivity/specificity and F1 score and f) evaluation of variable importance.

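### The dependent variable of the main analysis leaves a Barthel score of exactly 60 without a class

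*Protocol article*

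**What the plan says.** Under Statistical analysis, the Protocol article compares baseline and outcome variables between two Barthel groups, "dichotomized between dependent (BI < 60) and independent (BI > 60) patients", and cites reference 31 for the cut. The same section then specifies the multivariable step: "Model will be constructed with dichotomized Barthel index as dependent variable". The cut-off is not restated there.

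The Sample size calculation section gives this model its rank: "The sample size was carried out based on the main objective and analysis of the study". It again describes the logistic regression "with Barthel index dichotomize as dependent variable", without repeating the cut. The explanatory variables are "manual grip strength, EuroQoL-5D, NPRS, cross sectional area and thickness of the rectus femoris, STAI, TSK and BDI as explanatory variable". The size comes from the rule "100 + 50 × number of explanatory variables", by which "a sample of 500 subjects was recommended".

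No section puts a score of 60 in either group, gives a different threshold, or says how patients at 60 are to be handled.

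**The concern.** A two-way split has to classify every patient. This one omits the single score at which the classification changes, and the gap carries through each later step:

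- the t-tests, Mann-Whitney tests and Fisher tests between the two groups;
- the choice of adjustment variables, which depends on which baseline variables differ significantly in those tests;
- the fitting of the model in the 75% training set;
- the confusion matrix, ROC curve, sensitivity, specificity and F1 score in the 25% test set.

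The text allows two outcomes. If it is followed to the letter, patients at 60 have no value for the dependent variable and cannot enter any of these steps. They are then lost because of their outcome, and they are the patients closest to the boundary and hardest to classify. If the text is not followed to the letter, the analyst must pick a side. With no rule fixed beforehand, that choice can be made after the data are seen, and it can affect both the covariates selected and the accuracy reported.

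**Working it through.** **1. The gap.** A score is classified if it is below 60 or above 60. Scores of 0 to 100 in steps of five were tested against this condition (the five-point steps are an assumption, as the article does not describe the scoring). Only 60 fails. If either sign is changed to include equality, none fails.

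**2. The plan's own sample size.** The Sample size calculation section lists eight explanatory variables: grip strength, EuroQoL-5D, NPRS, cross-sectional area, thickness, STAI, TSK and BDI. The rule gives

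100 + 50 × 8 = 500,

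which reproduces the stated figure exactly. The rule has no term for patients without a classifiable outcome, so 500 contains no reserve.

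**3. Patients affected if the text is applied literally.** The share *s* scoring exactly 60 is not in the article, so a range is assumed. Unclassified = 500 × *s*; analysed = 500 × (1 − *s*); training and test sets are 75% and 25% of the analysed number. The last column is 500 / (1 − *s*), rounded up: the enrolment needed to keep 500 classified patients.

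| Assumed share at 60 | Unclassified | Analysed | Training | Test | Enrolment to keep 500 |
|---|---|---|---|---|---|
| 0% | 0 | 500 | 375 | 125 | 500 |
| 2% | 10 | 490 | 367.5 | 122.5 | 511 |
| 5% | 25 | 475 | 356.25 | 118.75 | 527 |
| 8% | 40 | 460 | 345 | 115 | 544 |

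Any share above zero takes the analysed number below the rule. Once 60 is assigned to a group, all 500 are classified and the requirement stays at 500.

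**4. Effect on the area under the ROC curve (AUC).** This was simulated, because the article gives no distribution. Assumptions: a normal underlying score, one normal predictor correlated 0.4 to 0.7 with it, 20% to 50% of patients below the cut, and 2% to 8% in the band that scores 60. The AUC with that band removed was compared with the AUC when the band is kept on one side.

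- Against placing 60 with the independent group, the AUC rises by about 0.003 to 0.02.
- Against placing 60 with the dependent group, it rises by about 0.003 to 0.03.

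The change was upward in every scenario.

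**5. Scale for comparison.** By the Hanley-McNeil formula, a test set of 125 with 20% to 50% dependent and a true AUC of 0.7 to 0.8 has a standard error of about 0.04 to 0.06. The shift in step 4 is smaller than that sampling error.

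**The case against.** The strongest reply is that this is a missing equals sign and nothing more. The article never says that patients at 60 will be left out. It plans to evaluate 500 patients and sizes the model on 500, and to dichotomise normally means to split everyone in two. The cited source may already settle the side. The share at 60 is assumed, the shift in AUC is below test-set noise, and the repair costs one symbol.

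Much of this stands. A reader might infer from the two strict inequalities that the investigators plan an outcome-based exclusion. The article does not support that: exclusion is the literal consequence of the wording, not a stated intention. Nor does it support a claim of serious bias in the accuracy measures. The article also does not use the term primary outcome; the Barthel split is the dependent variable of what it calls the main objective and analysis.

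A reader might also take this as grounds to object to dichotomising at all. That is a separate matter of preference. The cut is cited, and a binary outcome fits an aim framed as dependence versus independence and reported with classification measures.

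What the reply does not remove is the gap. The article states a definition and that definition is incomplete, so this is not a detail that a condensed article may leave to a fuller plan. The cited source cannot be checked here, and whatever it says, the printed text leaves 60 unassigned.

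**Conclusion.** The point holds as a faulty threshold in the dependent variable of the main analysis. That the definition omits 60, and that nothing elsewhere repairs it, follows from the text alone and needs no assumption.

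The size does rest on assumptions. With 2% to 8% of patients at exactly 60, literal application loses 10 to 40 of 500, against a rule that needs all 500. The upward shift in AUC is about 0.003 to 0.03 under the normal models described: consistent in direction, modest in amount. If the patients are kept, no number is lost, but their group is then chosen without a rule and possibly with the data in view. Either way the definition should be settled before analysis.

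**What to change.** Before any analysis, change one of the two inequalities so that 60 falls in one named group, consistent with the source cited for the cut (reference 31). State that the same definition applies to the univariate tests, the selection of adjustment variables and the logistic model. Repeat the model with 60 in the other group as a sensitivity analysis and report how many patients score exactly 60.

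The cost is one symbol, a sentence and one further model run. No data collection changes, and the required sample size stays at 500.

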### Sample characterization

Sociodemographic information (such as age, gender, level of education, perceived financial status, and frequency of social activity participation) is gathered using self-administered questionnaires as predictors of physical activity and fall history. These questionnaires are detailed in this paper.

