**Assessments**		
Manual grip strength	X	X
EQ-5D-5L	X	X
Barthel index	X	X
Trunk control test	X	X
BDI	X	X
VAS	X	X
GLIM	X	X
MRCSS	X	X
STAI	X	X
TSK	X	X
TUG	X	X
Adverse events		X

Timeline of procedures including enrollment, assessments, and ultrasound imaging. Abbreviations: EQ-5D-5L: EuroQol 5-dimensions 5-levels; BDI: Beck Depression Inventory; VAS: visual analogue scale; GLIM: Global Leadership Initiative on Malnutrition; MRCSS: Medical Research Council Sum Score; STAI: State-trait Anxiety Inventory; TSK: Tampa Scale of Kinesiophobia; TUG: Timed Up and Go test.

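### With only two classes of variable, the ordered sociodemographic items would naturally go to Fisher's exact test, which ignores the order of their levels

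*Protocol article*

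**What the plan says.** The Statistical analysis section of the protocol article describes two kinds of variable. Quantitative ones are checked for distribution and summarised by mean and standard deviation; qualitative ones are summarised by counts and frequencies. Patients are then "dichotomized between dependent (BI < 60) and independent (BI > 60) patients", and the two groups are compared by a t-test or Mann-Whitney test "for quantitative variables (depending on their distribution) and Fisher exact test for qualitative variables". No third class is given for ordered categories, and no variable is assigned to either class by name.

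The same section gives these comparisons a second use: "Model will be controlled by baseline variables with significant differences in univariate analysis".

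Sample characterization lists among the baseline items "level of education, perceived financial status, and frequency of social activity participation". The number of answer levels is not stated for any of them.

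**The concern.** These three items are graded. A mean and standard deviation, or a normality test, would make little sense for level of education or perceived financial status, whereas counts and frequencies are their usual summary. Followed as written, the two-class rule therefore sends them to Fisher's exact test.

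On a table of two groups by K levels, Fisher's test gives the same p-value however the levels are arranged. It spreads its sensitivity over K − 1 degrees of freedom, while a steady gradient between dependent and independent patients is mainly a one-degree-of-freedom shift. A rank or trend test concentrates on that shift.

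Two things are at stake. The reported comparison of dependent and independent patients is less sensitive on these items. And since significance in this step decides which baseline variables are adjusted for, a real social or socioeconomic gradient is more easily missed and left out of the controls.

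**Working it through.** **The plan's own figure.** The Sample size calculation uses "100 + 50 × number of explanatory variables". The explanatory variables are grip strength, EuroQoL-5D, NPRS, rectus femoris cross-sectional area, rectus femoris thickness, STAI, TSK and BDI, which makes eight: 100 + 50 × 8 = 500. This reproduces the stated sample. The article gives no power for the group comparisons, so there is none to reproduce.

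**Inputs.** From the article: N = 500 and a 0.05 significance level. Assumed, because the article does not give them: a two-sided test, 3 to 5 levels per item, a proportional-odds shift between the Barthel groups, and splits of 250/250 or 150/350.

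**Analytic check.** For a 1-df test with 80% power at two-sided 0.05, the noncentrality is (1.960 + 0.842)² = 7.85. The same noncentrality on 2, 3 and 4 df (3, 4 and 5 levels) gives 71%, 64% and 60% power. The loss is 80 − 71 = 9, 80 − 64 = 16 and 80 − 60 = 20 points.

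**Simulation.** There were 20,000 tables per setting. The tie-corrected Mann-Whitney test was set against the (K − 1)-df Pearson chi-square, used as a stand-in for the Fisher-Freeman-Halton test. The odds ratio was tuned to give rank-test power near 80%.

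| Levels | Split | Odds ratio | Mann-Whitney | Order ignored | Loss (points) |
|---|---|---|---|---|---|
| 3 | 250/250 | 1.59 | 79.9% | 71.2% | 8.6 |
| 3 | 150/350 | 1.67 | 80.7% | 72.2% | 8.5 |
| 4 | 250/250 | 1.58 | 80.8% | 65.6% | 15.2 |
| 4 | 150/350 | 1.63 | 79.7% | 64.5% | 15.2 |
| 5 | 250/250 | 1.58 | 79.9% | 59.4% | 20.5 |
| 5 | 150/350 | 1.65 | 80.8% | 60.9% | 19.9 |
| 5, skewed | 250/250 | 1.58 | 80.6% | 60.0% | 20.6 |
| 5, skewed | 150/350 | 1.64 | 79.8% | 57.8% | 22.0 |

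(Losses were computed before rounding.) With no true difference, both tests rejected in about 4.9% to 5.3% of tables, so the gap is not a difference in test size.

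**Is the stand-in fair?** A Monte Carlo Fisher-Freeman-Halton test was run on 1,000 tables in each setting above. Its power was within about 2.5 points of the chi-square figure. Against Mann-Whitney on those same 1,000 tables, it lost from 79.9 − 71.8 = 8.1 points (3 levels, 250/250) to 82.4 − 57.6 = 24.8 points (5 skewed levels, 150/350). This is the same picture with more simulation noise.

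**Where the loss shrinks.** At rank-test power near 95%, it is about 4 points for 3 levels, 8 for 4 levels and 11 to 13 for 5 levels. At an odds ratio of 2.5, it is at most 99.9 − 99.3 = 0.6 points for 3 to 5 equal levels. With two levels there is no order to lose.

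**Which variables the screening can affect.** The eight explanatory variables are named in advance in both Statistical analysis and Sample size calculation. Univariate significance decides only the additional baseline controls.

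**The case against.** The strongest reply is that the article never says graded items are qualitative. It names no variable in either class, it offers Mann-Whitney for quantitative variables that are not normal, and an analyst could score graded items and test them there. Variable typing is also often left to a fuller analysis plan, which is not shown. It stands that the classification is an inference and that a fuller plan may already settle it. But the two-class rule and its tests are stated, not omitted, and their natural reading leads to the less sensitive test.

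The sociodemographic items may have been recorded or collapsed as binary, and the article collects them as predictors of physical activity and falls, not expressly as candidates for the Barthel model. Both points stand as limits, although these items are still baseline variables under the screening rule.

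The power figures rest wholly on assumed inputs, and a proportional-odds shift favours the rank test; no non-monotone pattern was simulated. This stands too.

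The effect on the model is modest. Terms still pass through elastic net selection, BMI adjustment is planned separately, and leaving out a confounder because p exceeds 0.05 is a weakness of significance screening that a better test reduces but does not remove.

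A reader might also infer more than the article supports:

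- **That the EQ-5D-5L dimensions are caught.** Table 1 shows that the five-level version is used, but no item-by-item comparison is planned. EuroQoL-5D counts as one prespecified explanatory variable, which screening cannot remove.
- **That a loss of 10 to 20 points is a general property of the plan.** It is not; it depends on the number of levels and the effect size, as the working shows.
- **That ordered items would enter the logistic model as unordered categories.** The article does not say how they would be coded, so there is nothing to correct there.

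**Conclusion.** The point holds in limited form. On its natural reading, the two-class rule compares the three ordered sociodemographic items by a test that ignores their order. With 3 to 5 levels, a monotone shift and rank-test power near 80%, this costs about 9 to 22 points of power: roughly 9 for three levels, 15 for four and 20 to 22 for five. For large effects it is about 1 point or less, and for binary items nil. Levels, distributions, effect sizes and group split are all assumptions.

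The consequence is confined to the group comparisons and to the choice of baseline controls. The main explanatory variables and the sample size are untouched. It is a worthwhile refinement, not a threat to the study.

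**What to change.** In Statistical analysis, replace the two-class rule with three classes:

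- quantitative variables as now planned;
- ordered categories (level of education, perceived financial status, frequency of social activity) by the tie-corrected Mann-Whitney test or a Cochran-Armitage trend test;
- nominal and binary variables by Fisher's exact test.

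This takes one sentence. It needs no new data, patients or procedures, and Mann-Whitney is already in the plan. The small downside is that a rank or trend test is less sensitive to a non-monotone pattern, such as a difference confined to the middle levels. Such a pattern would still be visible in the frequencies that the plan already reports.
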